### Randomization

A stepped wedge, cluster randomized controlled trial design was chosen in which hospitals are allocated into geographical clusters and then randomized into two groups (intervention or control) within each of the five steps (Fig. 1). Twenty-five birthing hospitals included in the sampling frame have been grouped into 22 geographical clusters defined by postcode. As such, these clusters are the unit of randomization in this trial. The cluster randomization was completed using a random number generator in Excel. A member of the research team grouped the 25 hospitals into 22 clusters and labelled these clusters 1 to 22. A separate Excel spreadsheet was created with a column containing the numbers 1 to 22. No information about the corresponding hospitals was present in this document. The de-identified Excel file was given to our statistician, who was blinded to the corresponding cluster information. The random number generator was used to generate a number from 0 to 1 next to each number in the column containing the de-identified cluster data (numbers 1 to 22). The two columns were then sorted by the column containing the random number, from the smallest to the largest. Five steps are included in this stepped wedge design, each representing 6 months. During the first step, or the first 6 months, all clusters are controls. Allocation into the intervention or control group for the additional four steps is as described below. Using the sorted list provided by the statistician, the first five clusters were allocated to the intervention group in step 1. Once allocated to the intervention group, a cluster continues in the intervention group for the remainder of the trial. The remaining 17 clusters are allocated to the control group for step 1. For step 2, the six clusters that immediately follow the first five clusters in the list were allocated to the intervention group. In total, 11 clusters were allocated to the intervention group by step 2. The remaining 11 clusters were allocated to the control group. The next five clusters in the random number generator sorted list were allocated to the intervention in step 3. The remaining six clusters were allocated to the control group. The final six clusters were allocated to the intervention group in step 4. The intervention commencement will be staggered at 6 monthly intervals, and all clusters will receive the intervention by step 4.

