### Sample size calculation

The proposed sample size calculation is based on our primary hypothesis that the new model of care will result in a significant reduction in all-cause hospitalization in infants aged 0 to < 3 months of age. Our pilot data indicate that the approximate number of Aboriginal babies delivered in the birthing hospitals included in the sampling frame is 1,900 per year. We therefore anticipate approximately 4,750 Aboriginal births during the 30-month trial period. Of these, approximately 2,375 will be born in the control setting, and 2,375 in the intervention setting. All families delivering within the hospitals implementing the intervention will have the opportunity to participate in the trial. We estimate a 20 % refusal and loss to follow-up rate within the intervention group. Thus, we anticipate approximately 1,900 Aboriginal infants born over a 30-month period will be involved in the intervention. In total, approximately 4,300 Aboriginal infants will be followed up in the trial. Twenty-five hospitals with maternity units in WA comprise 22 distinct geographical clusters, with an average of 39 anticipated births per cluster per 6-month step. The average current prevalence of any (all cause) hospitalization in infants aged 0 to < 3 months is 31 %. Early data indicate that hospitalization rates range from 15 to 50 % across the clusters. Estimation of the study power requires calculation of the design effect, which, in the context of a stepped wedge design, is the factor which must be applied to the total number of subjects required in a similarly powered individual-level parallel group design to give the number of subjects per step in a stepped wedge design. We calculated the intracluster correlation (ICC) based on previous hospitalization rates. The calculated ICC of 0.017 was used in the Woertman et al. [28] formula to calculate the design effect with the outcome being 0.57. With 4,300 babies followed up over the 30-month period, the study will provide 80 % power to detect, at a significance level of *P* < 0.05, a reduction in prevalence of any early hospitalization of 31 % to 24.5 % because of the intervention.

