### Data analysis

Data analysis will be conducted on the basis of intention to treat, regardless of movement between clusters. The intervention effect will be estimated by the between-cluster (those awaiting the intervention and those receiving the intervention) and within-cluster (before and after) comparisons. An analysis of the primary outcome (any hospitalization in the first 3 months of life) will be conducted at the individual infant level and will use binary logistic regression incorporating generalized estimating equations (GEE) to account for the loss of independence due to clustering. The primary independent variable will be whether or not the baby received the intervention. This will give rise to an odds ratio for the effect of the intervention on the probability of early hospitalization. The analysis will adjust for individual covariates, for example, maternal age, which may differ between groups receiving or not receiving the intervention at a given step. Similar techniques will be used for comparison of emergency department presentations and immunization coverage.

A societal viewpoint will be taken for the economic evaluation where all costs and consequences to the mothers and the wider community will be considered. All direct (fixed and variable) costs will be considered and will include the monetary costs of the intervention and resources. Consequences will be measured as hospitalizations averted. Incremental direct costs will be calculated by comparing the costs generated by the intervention with the costs generated by the control arm of standard care. Incremental consequences will be calculated by comparing the number of hospitalizations in the intervention clinics with the number of hospitalizations in the control clinics. Incremental cost-effectiveness ratios (cost per infant hospitalization case averted) will be calculated by dividing the incremental direct costs by the incremental hospitalization cases averted. Sensitivity analysis (a method to determine the robustness of an assessment by examining the extent to which results are affected by changes in methods, values of variables or assumptions) will also be performed. Satisfaction with care will also be assessed descriptively. The process outcomes and implementation of the intervention will also be assessed descriptively.

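### The primary exposure is worded as the baby's receipt of the intervention, which read literally is as-treated and conflicts with the stated intention-to-treat basis

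*Protocol article*

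**What the plan says.** The Randomization section allocates 22 geographical clusters to crossover times: "As such, these clusters are the unit of randomization in this trial". The Data analysis section opens with the governing principle: "Data analysis will be conducted on the basis of intention to treat, regardless of movement between clusters". It then specifies an infant-level logistic regression with GEE for any hospitalization in the first 3 months, and names the exposure: "The primary independent variable will be whether or not the baby received the intervention".

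The Sample size calculation section splits the anticipated births by setting: "Of these, approximately 2,375 will be born in the control setting, and 2,375 in the intervention setting". It then makes one deduction, on one side only: "We estimate a 20 % refusal and loss to follow-up rate within the intervention group". From that it concludes that "we anticipate approximately 1,900 Aboriginal infants born over a 30-month period will be involved in the intervention", and it bases power on about 4,300 infants.

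Under Ethical issues, mothers in intervention clusters are asked for written consent to take part and to have evaluation data collected. Control clusters have no individual consent, and the investigators will apply for de-identified routine data instead. The Data collection section plans routine data for both groups but does not say whether non-consenting families in intervention clusters are covered.

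**The concern.** Under intention to treat, exposure follows allocation. Allocation here belongs to the cluster and the calendar step, not to the baby. An indicator of whether an individual baby received the intervention depends on something that happens after allocation, namely whether the family was reached and accepted, and that selection exists only after crossover. The control side has no matching step, because nobody there is asked.

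The intention-to-treat sentence does not close the gap. It is spelled out only for movement between clusters, not for families who decline.

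The primary odds ratio is at stake. If families who decline differ in infant risk from those who accept, comparing receivers with everyone else, or with control births only, mixes that difference into the effect estimate. The Background describes mobile and disadvantaged families with whom programs struggle to stay in contact, so a difference is plausible. The planned adjustment for covariates such as maternal age cannot be relied on to remove it.

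**Working it through.** **1. The plan's own figures**

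Design effect from the stepped-wedge formula that the protocol cites, with k = 4 steps, one baseline and one measurement per step, n = 39 per cluster-period and ICC = 0.017:

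- Correlation term: [1 + 0.017 x (156 + 39 - 1)] / [1 + 0.017 x (78 + 39 - 1)] = 4.298 / 2.972 = 1.446
- Multiplier: 3 x (1 - 0.017) / [2 x (4 - 1/4)] = 2.949 / 7.5 = 0.393
- Product: 0.569 (stated: 0.57)

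Two proportions, 31 % against 24.5 %, two-sided 5 %, 80 % power: 744 per arm, 1,488 in total. Then 1,488 x 0.57 x 5 periods = 4,241 (stated: about 4,300). Power at 4,300 is 80.6 %. The stated calculation reproduces and is not in dispute.

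**2. Who is counted**

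2,375 x 0.8 = 1,900 intervention infants, and 2,375 + 1,900 = 4,275. That is the number in the legend to Fig. 1 and is rounded to about 4,300 in the text. The 475 non-participants (2,375 - 1,900) are left out of the planned total. They are not moved to the control side.

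**3. Bias when the intervention does nothing**

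Inputs from the protocol: overall risk 31 %, 2,375 births per setting, up to 20 % not participating. Assumed: risk r among non-receivers, taken as 20, 40 or 50 %.

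- Receivers' risk = (0.31 - 0.2r) / 0.8
- Comparator if non-receivers are dropped = 0.31
- Comparator if they are coded unexposed = (2,375 x 0.31 + 475r) / 2,850

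| Assumed r | Receivers | Bias, dropped | Unexposed pool | Bias, coded unexposed |
|---|---|---|---|---|
| 20 % | 33.75 % | +2.75 pp | 29.17 % | +4.6 pp |
| 40 % | 28.75 % | -2.25 pp | 32.50 % | -3.75 pp |
| 50 % | 26.25 % | -4.75 pp | 34.17 % | -7.9 pp |

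The target difference is 31 - 24.5 = 6.5 pp. If infants are dropped, the 40 % and 50 % rows are 35 % and 73 % of that target. As odds ratios they are 0.90 and 0.79 (dropped) or 0.84 and 0.69 (coded unexposed), against a planned odds ratio of (0.245/0.755) / (0.31/0.69) = 0.72. Exposure by randomised cluster-period gives an odds ratio of 1.00 in every row.

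If only 10 % decline and r = 40 %, receivers' risk is (0.31 - 0.04) / 0.9 = 30 %, and the bias with dropping is -1.0 pp.

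**4. Price of analysing as randomised**

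If the full 20 % gain nothing (assumption), the intervention-condition risk is 0.31 - 0.8 x 0.065 = 25.8 %. With the same design effect of 0.57:

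| Non-receipt | Risk under intervention | Power, 4,300 | Power, 4,750 |
|---|---|---|---|
| 10 % | 25.15 % | 72 % | 76 % |
| 20 % | 25.8 % | 61 % | 65 % |

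At 20 % non-receipt, 80 % power would need 1,180 per arm before the design effect, so 2 x 1,180 x 0.57 x 5 = 6,726 infants.

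**The case against.** The best defence is that the sentence is loose wording for cluster condition. The Data analysis section speaks of clusters awaiting or receiving the intervention, the Trial design section has clusters, hospitals and clinics receive it, and the sample size section classes births by setting. Intention to treat is stated first and could be taken to govern what follows. An article may also leave the exact coding to a fuller document. On this reading the regressor is simply the cluster's condition attached to each infant.

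This stands as a possibility. A reader might infer that the trial is definitely committed to an as-treated analysis, and the text does not support that. But the charitable reading is nowhere stated. The one-sided 20 % deduction and the one-sided consent procedure point away from it, and towards analysing participating infants only. Nor is this a detail left for later, since the article names the primary exposure and an analysis plan that follows the sentence would inherit it.

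Three objections to the size also stand:

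- The 20 % combines refusal with loss to follow-up. A lost infant may have received the intervention, so refusal alone may be lower.
- The 15 to 50 % range in the protocol describes differences between clusters, not between decliners and accepters, so it only loosely anchors the assumed risks.
- The arithmetic is crude and ignores covariate, period and cluster adjustment.

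**Conclusion.** The contradiction is real and concerns the primary result, so the definition must be corrected. As written, the sentence allows at least two different estimands for one odds ratio, and the literal one is not protected by randomisation.

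The size is an illustration, not an estimate. With no true effect and up to 20 % non-receipt, assumed non-receiver risks of 20 to 50 % give a bias between +2.75 and -4.75 pp if non-participants are dropped, which is what the protocol's accounting implies. If they were coded unexposed it would lie between +4.6 and -7.9 pp.

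A reader might infer three stronger things that the document does not support:

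- That selection alone could exceed the whole 6.5-point target. This appears only when non-participants are pooled with controls at an assumed 50 % risk, and nothing in the protocol says they are pooled.
- That the bias must favour the intervention. Its direction depends on who declines, and the document gives no data on that.
- That receipt depends on how early or how safely a baby is discharged. No section says so.

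**What to change.** Define the primary independent variable as the randomised condition of the infant's birth cluster at the date of birth: control before the allocated crossover date and intervention from that date, whether or not the family was reached, consented or took up care coordination. Include all eligible births in both conditions through the routine linked data. Make actual receipt a labelled secondary analysis.

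The redefinition itself takes one sentence, but there are two further costs. First, the protocol describes the application for de-identified data without individual consent only for control clusters, so including non-consenting families in intervention clusters depends on linkage and ethics approval. If that is refused, the exclusion remains and should be declared as a limitation. Second, the estimate is diluted by non-acceptance, so the 80 % power statement has to be restated under explicit uptake assumptions. If the full 20 % gain no benefit, power is about 61 % with 4,300 infants or 65 % with all 4,750 births.

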### Trial design

This will be a stepped wedge, cluster randomized controlled trial (RCT) (Fig. 1). This is one of the most appropriate study designs for evaluating health system interventions [30]. Advantages include enhanced motivation from patients and health professional staff to participate because all clusters receive the intervention, the design is more ethical with quality improvement initiatives that are likely to involve more good than harm within the study population, and the study can reduce the required number of clusters and therefore requires less financial input [30, 31]. The intervention effect is estimated by the between-cluster (those awaiting the intervention and those receiving the intervention) and within-cluster (before and after) comparisons. All public birthing hospitals in WA have been grouped into 22 distinct geographic clusters and will be randomized in a “stepped” (staggered) order to receive our model of targeted early infant primary care or to continue with standard care. The trial will consist of a baseline period of 6 months, followed by four steps of 6-month duration. Five or six new clusters will receive the intervention at each step, and all hospitals and primary care clinics will receive the intervention by the end of the second year of the trial. The CONSORT cluster RCT and pragmatic trial guidelines will be followed [32, 33]. The trial profile is outlined in Fig. 2. The trial has been registered in the Australian New Zealand Clinical Trials Registry (ANZCTR) (Registration number ACTRN12615000976583).

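### The primary model as described names no 6-month step term, although exposed clusters rise from 0 to 22 of 22, so part of any secular trend would be read as intervention effect, and the model is not the one that was powered

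*Protocol article*

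**What the plan says.** The design has five 6-month periods (Trial design): "The trial will consist of a baseline period of 6 months, followed by four steps of 6-month duration". The Randomization section gives the roll-out. In the baseline period, "During the first step, or the first 6 months, all clusters are controls". At the first crossover, "the first five clusters were allocated to the intervention group in step 1". Six more follow: "In total, 11 clusters were allocated to the intervention group by step 2". Then "The next five clusters in the random number generator sorted list were allocated to the intervention in step 3", and the last six clusters cross over in the final period. Exposed clusters by period are therefore 0, 5, 11, 16 and 22 of 22.

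The Data analysis section describes the primary analysis of any hospitalization in the first 3 months as an infant-level logistic regression with GEE for clustering. Receipt of the intervention is the primary independent variable, and on other terms the section says: "The analysis will adjust for individual covariates, for example, maternal age, which may differ between groups receiving or not receiving the intervention". The effect is to draw on comparisons between clusters and on "within-cluster (before and after) comparisons". Similar techniques are announced for emergency department presentations and immunization coverage. No section names a step, period or calendar-time term, or mentions secular trend.

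The Sample size calculation section uses an ICC of 0.017 in a stepped-wedge "formula to calculate the design effect with the outcome being 0.57". It claims 80 % power for a reduction from 31 % to 24.5 % with 4,300 infants.

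**The concern.** In a stepped wedge, exposure and calendar time are tied together by design. Randomizing the order of crossover decides which clusters start early. It does not make exposed and unexposed infants contemporaneous. GEE deals with correlation within clusters, not with confounding by time, and maternal age or other individual covariates cannot stand in for period. Without a period term, a change in infant hospitalization that would have happened anyway is partly credited to, or held against, the intervention.

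At stake are the primary odds ratio and its P value, and the analyses of emergency presentations and immunization that follow the same approach. There is also an internal mismatch if the sample size rests on a step-adjusted analysis while the text describes an unadjusted one.

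**Working it through.** **Inputs.** Exposed clusters 0, 5, 11, 16, 22 of 22 (Trial design, Randomization). Risk 31 % against 24.5 %, ICC 0.017, 39 births per cluster per period, design effect 0.57, 4,300 infants, 80 % power, P < 0.05 (Sample size calculation). Sidedness is not stated, so I take two-sided.

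**1. The plan's own figures.** The article does not print the formula. The usual stepped-wedge form is

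DE = [1 + ρ(ktn + bn − 1)] / [1 + ρ(ktn/2 + bn − 1)] × 3(1 − ρ) / [2t(k − 1/k)].

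With k = 4 crossovers, t = 1, b = 1, n = 39 and ρ = 0.017:

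- numerator: 1 + 0.017 × 194 = 4.298
- denominator: 1 + 0.017 × 116 = 2.972
- last factor: 3 × 0.983 / (2 × 3.75) = 0.3932
- DE = 4.298 / 2.972 × 0.3932 = 0.569 (stated 0.57)

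An individually randomized comparison of 31 % with 24.5 % needs 1,488 infants. Then 1,488 × 0.57 × 5 periods = 4,241, close to the stated 4,300. With 4,300 infants the power is 80.6 %. The stated figures reproduce.

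**2. How far exposure and time coincide.** Number the periods 0 to 4.

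- Exposed cluster-periods: 5 + 11 + 16 + 22 = 54 of 110. Mean period (5×1 + 11×2 + 16×3 + 22×4) / 54 = 163/54 = 3.02.
- Control cluster-periods: 22 + 17 + 11 + 6 = 56. Mean period (17×1 + 11×2 + 6×3) / 56 = 57/56 = 1.02.
- Gap: 2.00 periods, or 12 months. The correlation of exposure with period is 0.71.
- Within a cluster that crosses over at period s, the gap is (s + 4)/2 − (s − 1)/2 = 2.5 periods, or 15 months, whatever s is.

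**3. Which analysis has 80 % power.** Generalized least squares for the actual 5/6/5/6 roll-out, exchangeable correlation, 39 births per cell, mean risk (0.31 + 0.245)/2 = 0.2775, power = Φ(0.065/SE − 1.96):

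| Model | SE | Power |
|---|---|---|
| With period terms | 0.0231 | 80.4 % |
| Without period terms | 0.0147 | 99.3 % (nominal) |

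At 4,750/110 = 43.2 births per cell, before refusals, the figures are 83.9 % and 99.6 %.

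**4. Share of a linear trend absorbed without period terms.** Under working independence it is the gap in mean period over the four-period span, 2.00/4 = 50 %. Under exchangeable correlation with ICC 0.017, projecting the trend on the model gives 59 %. No trend is given in the article, so the sizes below are assumptions. Type I error is Φ(−1.96 − b/SE) + 1 − Φ(1.96 − b/SE), with b the spurious effect and SE 0.0147:

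| Fall, first to last period | Spurious effect (exchangeable) | Nominal type I error |
|---|---|---|
| 1 point | −0.6 points | 7 % |
| 2 points | −1.2 points | 13 % |
| 4 points | −2.4 points | 36 % |
| 8 points | −4.7 points | 89 % |

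A rise gives the same sizes with the opposite sign. A 4-point rise would shrink a true 6.5-point reduction to about 6.5 − 2.4 = 4.1 points.

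**5. Check by simulation.** Logistic GEE, exchangeable, 22 clusters × 5 periods × 39 infants, no true effect, 300 runs per scenario:

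| Fall over the trial | Without period terms | With period terms |
|---|---|---|
| None | OR 1.00, rejects 7 % | OR 1.00, rejects 8 % |
| 4 points | OR 0.89, rejects 39 % | OR 1.00, rejects 9 % |
| 8 points | OR 0.79, rejects 89 % | OR 1.00, rejects 5 % |

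Rejection of 7 to 9 % where no bias is expected reflects the robust variance with only 22 clusters, plus Monte Carlo error.

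**The case against.** The best defence is that a journal article condenses the plan. It names a primary independent variable, which implies others, and introduces covariates only by example. It never says that time is left out. The covariate sentence ends by referring to differences within a step, which shows that the authors had step in mind. The remark on before-and-after comparisons repeats a general description of the design given under Trial design and need not mean a separate unadjusted analysis. The power figure can also be read as a sign that a step-adjusted model was always intended.

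Part of this stands. The article does not show that the investigators mean to leave step out, and an unseen analysis plan may contain it. But the section does not leave the model open: it gives outcome, link, correlation method, exposure variable and type of covariate. The reference to step says when individual covariates may differ and does not put step in the model. Period is a structural term of this design, and anyone following the text would fit a time-confounded model.

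Three stronger inferences are not supported:

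- **That the whole of a secular trend becomes intervention effect.** The share is about 50 to 59 %.
- **That the false-positive rate is far above 5 % whatever happens, or that the bias must favour the intervention.** Both depend on a trend that the article does not report, and a rise would work against the intervention.
- **That the article documents a trend through concurrent system change.** The 48-hour birth-data system dates from 2013, and recruitment starts in 2016. Nothing in the article links electronic health records or Primary Health Networks to a change in infant hospitalization.

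**Conclusion.** The point holds as a defect in the model as described. The absence of a named step term and the roll-out counts come straight from the text. The mismatch with the sample size needs no assumption about trend: at 39 births per cell and two-sided 5 %, the stated 80 % is reached with period terms and not without them. The share absorbed assumes a linear trend common to all clusters. The type I error figures are also conditional on assumed falls. They illustrate sensitivity and do not predict what this trial will show. Small trends (1 to 2 points over 30 months) do modest harm to type I error. A 4-point fall, against a target effect of 6.5 points, does a great deal. Since the size and sign of the trend are unknown beforehand, the described model cannot by itself attribute a change to the intervention.

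**What to change.** In the Data analysis section, state that the primary GEE contains the intervention indicator, categorical 6-month step (four indicators for the five periods) and the individual covariates. State that the similar models for emergency department presentations and immunization coverage contain the same step terms, and that before-and-after comparisons are interpreted only after adjustment for step. How the intervention indicator is defined is a separate question that this change leaves alone.

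The cost is one or two sentences. Period follows from the infant's date of birth, so no new data are needed, and nothing is lost against the stated 80 % power, which already corresponds to a step-adjusted analysis. If an existing analysis plan includes step, the change only brings the article's description into line with it.

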### Data collection

Outcomes will measure the impact of the intervention from a systems perspective, including the quality of care, healthcare utilization and cost. Outcomes will also measure the process of the intervention from family and healthcare professional perspectives.

Information from routine data capture systems (midwives notification system, hospital morbidity database, emergency department database, Australian Immunisation Register (ACIR) database, and the Commonwealth Medical Benefits System (MBS) database) will be collected from both the control and intervention groups. These data will include the following: (i) sociodemographic data: obstetric history, age, sociodemographics, medical history, morbidities, birth weight, gestational age, Apgar score, and discharge date; (ii) hospitalization data from all WA hospitals on all-cause hospitalization and emergency department presentations; (iii) immunization data from ACIR (date of first and second doses of hepatitis B and date of first dose of DTP containing vaccine) from birth until the baby reaches 3 months of age; and (iv) Medicare data from the MBS (Date of Medicare registration and dates of child health checks (item number 715)) from birth until the baby reaches 3 months of age.

Economic evaluation will compare outcomes between the intervention and control groups. Consequences will be measured as the health gains from the child health assessments and immunizations received. Short-term health gains include reduced emergency department presentations and hospital admissions during the first 3 months of life. Long-term health gains include improved child neurodevelopment (especially speech delay, concentration, learning and educational outcomes) and reduced infectious disease (including gastroenteritis, Haemophilus influenzae type b (Hib), pneumococcal disease and pertussis).

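### The cost-effectiveness ratio rests on numbers of hospitalizations rather than adjusted per-infant risks, so unequal group sizes and calendar trend can enter its denominator

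*Protocol article*

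**What the plan says.** The economic evaluation in the protocol article's Data analysis section fixes the effect side of the ratio: "Incremental consequences will be calculated by comparing the number of hospitalizations in the intervention clinics with the number of hospitalizations in the control clinics". The ratio itself "will be calculated by dividing the incremental direct costs by the incremental hospitalization cases averted". The paragraph names no rate per infant and no allowance for step or cluster. It also does not refer to the GEE estimate described just above it.

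The Sample size calculation section gives the expected group sizes. Births are split equally: "Of these, approximately 2,375 will be born in the control setting, and 2,375 in the intervention setting". The loss is not: "We estimate a 20 % refusal and loss to follow-up rate within the intervention group". The result is that "we anticipate approximately 1,900 Aboriginal infants born over a 30-month period will be involved in the intervention".

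The Ethical issues section explains the asymmetry. Mothers in intervention clusters are asked to consent to collection of evaluation data, while control data come from routine linkage without individual consent. Under the Trial design and Randomization sections, every cluster starts as control and ends as intervention.

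**The concern.** In a stepped wedge trial, control clinics and intervention clinics are the same clinics at different times. The number of hospitalizations in each condition depends on three things besides the intervention: how many infants are counted, which clusters they come from, and when they were born. A comparison of counts removes none of these.

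On the article's own figures, fewer infants may be counted under intervention than under control. Fewer admissions would then follow from fewer infants, and a programme with no effect would appear to avert hospitalizations and would receive a finite cost per case averted. Calendar trend is a second, separate route for error. Cost effectiveness is a declared aim of the study, so the quantity that goes into the ratio should be one that is zero when the intervention does nothing.

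**Working it through.** **Inputs.** Sample size calculation: 4,750 births in 30 months, 2,375 per condition; 20 % refusal and loss on the intervention side; 31 % hospitalized before 3 months of age; target 24.5 %; ICC 0.017; design effect 0.57; 39 births per cluster per step. Randomization: 22 clusters, five periods, with 5, 6, 5 and 6 clusters crossing over.

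**The plan's own figures first.**
- Intervention infants: 2,375 × 0.8 = 1,900. Total: 2,375 + 1,900 = 4,275, which is the Fig. 1 figure and rounds to the 4,300 followed up.
- Design effect, from the stepped wedge formula with k = 4 steps, t = 1, b = 1, n = 39 and ρ = 0.017: [1 + ρ(ktn + bn − 1)] / [1 + ρ(ktn/2 + bn − 1)] × 3(1 − ρ) / [2t(k − 1/k)] = (4.298 / 2.972) × (2.949 / 7.5) = 0.569. The article states 0.57.
- Individually randomized trial, 31 % against 24.5 %, 80 % power, two-sided 5 % (sidedness is assumed): 744 per arm, 1,488 in total. Then 1,488 × 0.57 × 5 = 4,241, or 4,417 with continuity correction; the article states 4,300. The sample size reproduces, so 4,300 rests on 2,375 control and 1,900 intervention infants.

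**Count comparison with no intervention effect and no time trend.** Apparent cases averted = p × (control infants − intervention infants). A per-infant comparison gives 0.31 − 0.31 = 0 in every row.

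| Infants counted | Control | Intervention | Apparent cases averted |
|---|---|---|---|
| Followed up, article's numbers | 2,375 | 1,900 | 0.31 × 475 = 147 |
| All births, equal split | 2,375 | 2,375 | 0 |
| All births, split by cluster-periods | 2,418 | 2,332 | 0.31 × 86.4 = 27 |
| Cluster-period split with 20 % loss | 2,418 | 1,865 | 0.31 × 552.7 = 171 |

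The cluster-period split comes from the roll-out. Control clusters per period are 22, 17, 11, 6, 0 (sum 56) and intervention clusters are 0, 5, 11, 16, 22 (sum 54). So 4,750 × 56/110 = 2,418, 4,750 × 54/110 = 2,332, and 2,332 × 0.8 = 1,865.

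**Count comparison at the target effect.**
- Followed-up infants: 2,375 × 0.31 − 1,900 × 0.245 = 736.25 − 465.5 = 270.75.
- Per-infant basis: 1,900 × (0.31 − 0.245) = 123.5.
- Quotient: 270.75 / 123.5 = 2.19.
- All births, equal split: 2,375 × 0.065 = 154.4 by either route, so there is no distortion from group size.

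**Calendar time.** Mean control period = (22×1 + 17×2 + 11×3 + 6×4) / 56 = 113/56 = 2.02. Mean intervention period = (5×2 + 11×3 + 16×4 + 22×5) / 54 = 217/54 = 4.02. The gap is two 6-month periods, about 12 months. The documents give no secular trend. If the risk drifted by 0.5 to 1 percentage point per period (an assumption), the unadjusted contrast would shift by 1 to 2 points, or 19 to 38 cases per 1,900 infants, in either direction.

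**The case against.** The strongest reply is that this is a one-sentence summary in a condensed article. It speaks of comparing numbers and does not say that unscaled totals will be subtracted. Scaling, adjustment and intervals could sit in a fuller economic plan, and the same section opens with intention to treat and with between- and within-cluster comparisons. This limits how confident one can be about what will be done. It does not remove the point, because the article names the quantity to be compared, and that quantity is a count. A later plan that followed the sentence faithfully would carry the fault.

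Several stronger readings are tempting and are not supported:

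- *That 147 spurious cases are certain.* The figure needs all control births but only the followed-up intervention infants. The consent arrangement and the 4,300 total favour that reading. Intention to treat, and hospitalization data from routine systems for both groups, favour counting all births, which gives 0 to 27. The article allows both.
- *That the 147 reflects calendar confounding.* It comes from group size alone.
- *That the error always favours the intervention.* A trend can run either way. With all births counted, the 27-case artefact equals 27/2,332 = 1.15 percentage points, so a rise of about 0.6 points per period would reverse the sign.
- *That cost per case averted is understated 2.2-fold.* That holds the numerator fixed. The article also compares costs between conditions, so totals from unequal groups would move the numerator too.
- *That the ratio contradicts the stated viewpoint and definition of consequences.* "A societal viewpoint will be taken for the economic evaluation" is followed by a ratio in direct costs, and the Data collection section lists implementation costs, but as items included rather than as a complete list. Likewise "Consequences will be measured as the health gains from the child health assessments and immunizations received" is followed there by reduced hospital admissions as a short-term gain, which overlaps with hospitalizations averted. Neither carries this point.
- *That health services will decide on this ratio.* The Discussion refers to the study's results as a whole.

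**Conclusion.** The point holds. As written, the denominator of the cost-effectiveness ratio is a comparison of hospitalization counts between conditions that may differ in size and do differ in calendar time.

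The group-size artefact under no effect is about 147 infants on the article's expected numbers followed up, 171 if the cluster-period split is also applied, and 0 to 27 if all births are counted. At the target effect the followed-up count gives about 271 against 124. These figures assume that each infant is either hospitalized or not, at 31 % under control. The article's sentence refers to hospitalizations, so repeat admissions would change them. The effect on the ratio also depends on how total costs are compared, which the article does not settle.

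The calendar component is real in structure, with a gap of about 12 months, but its size and direction are unknown.

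The primary analysis and the sample size are not affected by this point. What is affected is a declared secondary evaluation.

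**What to change.** Replace the count comparison in the economic evaluation with the following:

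1. State which infants are counted, and use the same set for effects and costs.
2. Define hospitalizations averted as the period- and cluster-adjusted per-infant risk difference, multiplied by the number of infants in intervention cluster-periods. The risk difference can be obtained by marginal standardisation from the primary GEE logistic model. The described model names no step term, so one must be included.
3. State whether a case is an infant with any hospitalization or an admission. The risk difference above serves the former; if admissions are meant, use an adjusted rate difference per infant.
4. Express incremental cost per infant on the same denominator, with the same adjustment for period and cluster.
5. Give an interval for the ratio that respects the clustering, for example by resampling whole clusters.

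The hospitalization data needed are already planned. The cost is a little more analysis work and possibly a less favourable ratio.
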